### Sample size calculation

2.3

An *a priori* power analysis was performed using JASP (version 0.19.2) to estimate the required sample size for detecting a between-group difference in biomarker levels with adequate statistical power. Assuming a one-sided independent samples *t*-test, a medium effect size (Cohen's |*δ*| = 0.5), a Type I error rate (*α*) of 0.05 and a target power (1−*β*) of 0.95, the analysis indicated that a minimum of 66 participants in the ICP-exposed group and 132 in the unexposed group would be required to achieve an actual power of 0.952.

These parameters were selected to align with the study's directional hypothesis that intrahepatic cholestasis of pregnancy is associated with poorer respiratory outcomes and higher biomarker levels. A 2:1 unexposed-to-exposed ratio was adopted to address the lower expected incidence of neonates with maternal ICP, providing greater statistical precision while also enhancing generalizability and minimizing bias, without placing disproportionate demands on recruitment. Also, the higher power threshold of 0.95 was chosen to ensure adequate sensitivity for detecting clinically meaningful biomarker differences, which represent a novel co-primary objective and a central component of the study's design.

This configuration provides robust power to detect moderate effect sizes over 0.5 with high reliability, acknowledging that smaller effects (|*δ*| ≤ 0.25) are associated with a substantially reduced probability of detection. Accordingly, a minimum of 198 neonates will be enrolled to meet the sample size requirements established by the power analysis.

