### Sample collection

2.5

Venous blood samples (2 mL) will be collected from eligible neonates into gel tubes containing a clot activator, adhering to institutional safety protocols and standard procedures for biological sample handling. Blood collection will be performed within the first 24 h of life, followed by a second sample at 48–72 h, contingent upon clinical stability and the presence of an indication for additional routine laboratory investigations. In neonates with longer hospitalizations, a third sample may be obtained on day 7 of life.

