### Statistical analysis

2.8

Statistical analysis will be performed using JASP 0.19.2. Frequency analysis will be performed using contingency tables. Group differences in the incidence of RDS and the need for surfactant therapy will be assessed using the chi-squared test or Fisher's exact test, where expected cell counts are less than five. Differences in mortality will be evaluated descriptively using odds ratios (ORs), and if event frequency permits, time-to-event analysis may be considered. In addition, time-to-event outcomes such as time to first surfactant dose, time to intubation and time to second surfactant administration will be analyzed using Kaplan–Meier curves and compared using the log-rank test, with Cox regression models applied where appropriate.

Serum biomarker levels indicative of lung injury will be compared between groups at each time point using the Student's *t*-test for normally distributed data or the Mann–Whitney *U* test when normality is not assumed. To assess longitudinal trends in biomarker levels, repeated-measures ANOVA or linear mixed-effects models will be employed, depending on data distribution and completeness. For non-parametric repeated data, the Friedman test may be used. Normality and homogeneity of variances will be tested using the Shapiro–Wilk and Brown-Forsythe tests, respectively. A significance level of 0.05 will be used for all analyses. For normally distributed biomarker data, standardized mean differences between groups will be reported as Cohen's d and Glass's delta. To account for potential residual confounding, gestational age at birth, matched during enrollment, will additionally be included as a covariate in relevant statistical models and stratified analyses may be performed to explore outcome differences across gestational age subgroups.

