Nevertheless, certain limitations are anticipated. As a single-center study, generalizability may be limited, though the use of carefully matched controls mitigates this to some extent. Practical constraints may occasionally lead to delays in sample centrifugation, in which case samples will be stored at 2–5 °C in a dedicated medical-grade refrigerator. Sample hemolysis or insufficient serum volume may affect the ability to test all biomarkers, however these deviations will be documented transparently and addressed in the final analysis. Although early neonatal death is expected to be rare, it may act as a competing risk for outcomes such as RDS. Therefore, all mortality events and their timing will be recorded and considered in the interpretation of respiratory outcomes.

Ethical considerations have been fully integrated into the study design. Informed consent is obtained only after obstetric teams confirm an imminent delivery and before administration of anesthesia. Mothers are given time and autonomy to ask questions and are clearly informed of their right to decline or withdraw participation, without any impact on neonatal care. Blood samples are collected exclusively during procedures already indicated for clinical care, otherwise, if no clinical indication exists or the neonate's condition prohibits collection during a designated window, the sample is skipped and the reason will be included in the study's final reporting.

The CHOLE-RESP study has the potential to significantly advance the field by providing the first structured clinical and biochemical assessment of neonatal respiratory outcomes following ICP exposure. If the study confirms a measurable link between bile acid exposure and pulmonary injury, this could support the development of risk-based screening tools and tailored respiratory management strategies. Moreover, growing evidence from metabolomic and proteomic research suggests that intrahepatic cholestasis of pregnancy is associated with complex molecular signatures extending beyond bile acid concentrations alone (15, 16). Within this framework, the present study lays the groundwork for future multicenter validation efforts, broader biomarker profiling and the integration of hypothesis-generating omics approaches aimed at refining risk stratification and improving outcomes in this understudied neonatal population.

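### Biomarker samples exist only where care calls for blood, so the co-primary comparison is open to selection bias of unknown size, and two of the permitted longitudinal methods make this worse

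*Protocol article*

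**What the plan says.** **Status of the endpoint.** Sections 2.2 and 2.3 of the Protocol article list the biomarker profile among the primary objectives and call it co-primary. The sample size rests on it alone: 66 exposed and 132 unexposed neonates for a stated power of 0.952. The 198 to be enrolled equal the 198 who need a measured value.

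**When blood is taken.** Section 2.5 gives the first sample, within 24 h, no condition of its own. The 48–72 h sample is "contingent upon clinical stability and the presence of an indication for additional routine laboratory investigations". For the last window: "In neonates with longer hospitalizations, a third sample may be obtained on day 7 of life". The Discussion then extends the indication rule to every window: "Blood samples are collected exclusively during procedures already indicated for clinical care, otherwise, if no clinical indication exists", or the neonate's condition prevents collection, the sample is skipped and the reason reported. Section 4 also limits sampling to routine draws. It adds that when the neonate's condition prevents timely collection, sampling is deferred to the next scheduled test within the window.

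**How biomarkers are analysed.** Section 2.8 says levels "will be compared between groups at each time point" by Student's t-test or Mann–Whitney. Longitudinal trends use repeated-measures ANOVA or a linear mixed-effects model, depending on distribution and completeness. It adds: "For non-parametric repeated data, the Friedman test may be used". Gestational age is a covariate in relevant models.

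**The concern.** A neonate contributes a biomarker value only if clinical circumstances led to a draw. A well term control may have no indicated draw, an unstable neonate may miss the 48–72 h window, and day 7 covers only those still in hospital. The study's hypothesis is that cholestasis causes respiratory illness. Its own retrospective data on preterm infants (Discussion) report more ventilation, CPAP and surfactant use and longer support in exposed infants. Sampling may therefore be a consequence of exposure, and a comparison among the sampled conditions on that consequence. Matching at enrolment on gestational age, birthweight and sex does not protect the subset that happens to be sampled.

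If the sampled controls are sicker than controls in general, the observed difference is pulled away from the true one. The limitations in the Discussion mention hemolysis, low serum volume and delayed centrifugation, but not selective sampling. Missing samples also reduce power, and the enrolment target makes no allowance for them.

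**Working it through.** **1. The plan's own power.** Inputs from section 2.3: "Assuming a one-sided independent samples *t*-test, a medium effect size" of 0.5, "a Type I error rate (*α*) of 0.05", and groups of 66 and 132.

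- Noncentrality = 0.5 × √(66 × 132 / 198) = 0.5 × √44 = 3.317, with df = 66 + 132 − 2 = 196.
- The one-sided 5% critical value is 1.653, and the noncentral t gives power 0.9516. The stated 0.952 is reproduced.
- 65/130 gives 0.949, so 66/132 is the smallest 2:1 size that reaches 0.95.

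**2. Loss of numbers only.** Here sampling is unrelated to illness. The fractions are assumed, because the document gives none.

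| Sampled, both groups | n exposed / unexposed | Noncentrality | Power |
|---|---|---|---|
| 100% | 66 / 132 | 3.317 | 0.952 |
| 80% | 53 / 106 | 0.5 × √(53 × 106 / 159) = 2.972 | 0.906 |
| 60% | 40 / 79 | 0.5 × √(40 × 79 / 119) = 2.577 | 0.820 |

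**3. Sampling driven by severity.** All inputs are assumptions except the exposed share, which is 66/198 = 1/3. With X = 1 for exposed, severity is S = 0.5·X + e, with e standard normal. The biomarker has within-group SD 1 and within-group correlation 0.5 or 0.7 with S. A neonate is sampled if S + 0.5 × (standard normal noise) exceeds a common cut-off set by the overall fraction. The observed difference is divided by the pooled SD among those sampled. Results are from simulation, shown as correlation 0.5 / 0.7.

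| Sampled overall | Exposed / unexposed sampled | True 0.5 observed as | True 0 observed as | Power for true 0.5 |
|---|---|---|---|---|
| 90% | 95% / 88% | 0.46 / 0.45 | −0.05 / −0.08 | 0.90 / 0.89 |
| 80% | 88% / 76% | 0.44 / 0.43 | −0.08 / −0.12 | 0.85 / 0.83 |
| 50% | 62% / 44% | 0.40 / 0.38 | −0.13 / −0.20 | 0.62 / 0.57 |
| 25% | 35% / 20% | 0.38 / 0.34 | −0.17 / −0.25 | 0.37 / 0.32 |

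**4. Sensitivity to the assumptions.** A second model fixes the sampled fraction in each group, with severity distributed alike in both and correlated 0.7 with the tendency to be sampled.

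- With 60% sampled in both groups, a true 0.5 stays at 0.50, so there is no bias.
- With 90% of exposed and 60% of unexposed sampled, it falls to 0.41 (biomarker–severity correlation 0.3) or 0.34 (correlation 0.5).
- With 90% and 40%, it falls to 0.34 or 0.23.

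The bias thus needs a difference between groups in sampling or severity, and its size depends strongly on how large that difference is.

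**5. The longitudinal methods.** This step needs no assumed rates. In standard form, repeated-measures ANOVA and Friedman use only subjects measured at every time point. Under section 2.5 that means neonates with a day 7 sample, who are the longer stays. Friedman ranks time points within each subject and has no between-group factor, so it cannot compare exposed with unexposed.

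**The case against.** The plan is better than a quick reading suggests. Section 2.8 already names a linear mixed model and ties the choice to completeness. Such a model uses partial series under missing at random. A reader might infer that the longitudinal result must describe long-stay neonates only, but the document does not fix that. Friedman is only something that may be used, for trends, and Mann–Whitney remains the non-parametric test between groups. Gestational age is a covariate, the Discussion says models also include sex and perinatal infection, and skip reasons will be reported. Section 4 allows deferral within the window. The first sample carries no stability condition in section 2.5, and nothing suggests that only a quarter or half of neonates will be sampled at 24 h.

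These points soften the concern but do not remove it. A mixed model cannot recover neonates who were never sampled or correct for sampling that depends on unmeasured severity. Gestational age does not capture postnatal illness. Reporting skip reasons discloses selection without correcting it.

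A reader might also infer that the biomarker result will be distorted or even reversed. The documents give no sampling rates, and with a true 0.5 every scenario above stays positive; negative values arise only when the true effect is zero. The retrospective data report that RDS itself was not consistently more frequent, so the assumed 0.5 SD severity shift is not established.

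Detailed missing-data handling may sit in an analysis plan that is not shown, and its absence is not the point. The sampling rule and the named tests are stated in this article.

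**Conclusion.** The concern holds as a vulnerability, not as a demonstrated distortion. The sampling rule makes the existence of a biomarker value depend on illness that the study ties to exposure, and the planned group tests use only those sampled. Bias follows if sampling or severity differs by group. Its size and direction cannot be settled from the document. In the main illustration, a true 0.5 SD appears as about 0.43–0.46 at 80–90% sampled and 0.34–0.40 at 25–50%, and a true null as about −0.05 to −0.25.

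Two parts do not depend on those assumptions. The 0.952 power holds only if all 66 and 132 neonates have a measured value. And Friedman, as a permitted method, cannot answer the between-group question.

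**What to change.** - Name the sample within 24 h as the single confirmatory biomarker time point. It is the least conditional of the three, although not free of selection.
- Commit to one linear mixed model, on the log scale if concentrations are skewed, with group × time, all available samples, gestational age and the recorded baseline covariates. Delete repeated-measures ANOVA and Friedman.
- Label the 48–72 h and day 7 comparisons as descriptive in sampled neonates. Show the sampled fraction and skip reasons by group and window.
- Add inverse-probability-of-sampling weighting as a sensitivity analysis only, using variables that section 2.7 already collects, such as Apgar scores, respiratory support and NICU admission. State that it cannot represent neonates with almost no chance of a draw, and that it may widen intervals considerably.
- State in section 2.3 that the 0.952 assumes complete sampling, and give the power at lower fractions.
- Reconcile the Discussion (sample skipped) with section 4 (sample deferred within the window), and both with the unconditional first sample in section 2.5.

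This needs no extra blood draws and no new variables. The cost is that the later time points lose confirmatory status and the stated power becomes less favourable.

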## Ethics and dissemination

4

The CHOLE-RESP study protocol received approval from the Ethics Committee of the “[name]. Panait Sîrbu” Clinical Hospital of Obstetrics and Gynecology (Approval No. 34/15.10.2024) and was registered on ClinicalTrials.gov (NCT06679972).

Written informed consent is obtained from the legal guardians of all participants after the obstetric team confirms the likelihood of delivery within the next 24 h and prior to the administration of anesthesia. Mothers are fully informed of the study objectives and procedures, and reassured of their right to decline or withdraw participation at any point without consequences to the medical care provided to their newborn.

Biological samples are collected only during routine clinical blood draws to minimize patient discomfort. In cases where the clinical condition of the neonate precludes timely collection, sampling is deferred to the next scheduled blood test within the collection window. Deviations from the planned sampling protocol, such as refrigeration of unprocessed samples or collection of hemolysed or insufficient serum, are documented and will be transparently addressed in the final manuscript.

Study findings will be disseminated through presentations at scientific conferences and submitted for publication in peer-reviewed journals. Preliminary results will be shared upon completion of the initial recruitment target. No personal identifying information will be published, and all data will be anonymized prior to dissemination.
